### Intervention

Patients in the experimental study arm enter a stepped care programme including 1) watchful waiting, 2) guided self-help via Internet or a booklet, 3) face-to-face problem solving treatment, 4) specialised psychological interventions such as cognitive behavioural therapy and/or antidepressant medication.

The basic proposition of stepped care is that all patients are offered the same low intensity (evidence-based) treatment as a first step. Only those patients, who do not recover, step up to a more intensive treatment. The HADS score is used to determine stepped-up levels of care. Stepping up to the next treatment level is indicated when a participant’s HADS-A or HADS-D score exceeds 7. The care coordinator controls the process, monitors the symptoms, and makes sure the patient steps up if necessary.

The stepped care programme in the present project includes the following four steps.

#### Step 1: Watchful waiting

In the first step it is agreed on not to start intervention yet, but to wait for further development of symptoms. Because part of the patients recovers spontaneously [18] ‘watchful waiting’ is included in the multidisciplinary guideline on depression as first treatment step. Duration of the watchful waiting period in the present project including cancer patients is set on 2 weeks.

#### Step 2: Guided self-help via Internet or a booklet

If there is no spontaneous recovery after 2 weeks, the care coordinator contacts the patient for one counselling session in which the self-help programme is introduced. As intervention the existing programme “Allesondercontrole” or the web based programme “Allesondercontrole” (http://allesondercontrole.psy.vu.nl) is used. “Allesondercontrole” is a brief intervention for problem-solving based on self-examination. “Allesondercontrole” is already available. The website is currently only used for research purposes and both international and national research has shown that this intervention is effective in depression and anxiety [19]. The intervention is based on problem-solving therapy, which has been proven to be effective in several randomized controlled studies [20], also when delivered via the Internet. A recent meta-analysis by our group found that the effects of Internet-based treatments of depression and anxiety disorders are as large as those of face-to-face treatments [21]. The intervention “Allesondercontrole” takes 5 weeks. In that period respondents describe what they think is important in their lives, make a list of their problems and concerns, and divide these into three categories: unimportant problems (problems which are not related to what is important in their life), important and amenable problems (these are solved through a six-step procedure of problem-solving), and important but unsolvable problems (such as having a serious disease like cancer); for each of the amenable problems the respondent makes a plan). Trained coaches guide the patients through this process. The coaching consists of brief, weekly contacts by email or by telephone, which takes about 10 to 15 minutes per week. The total coaching time is 1 to 1.5 hours per patient (estimation based on our previous trial). Coaching is not aimed at developing a patient-therapist relation but is only meant to give support in working through the self-help method.

#### Step 3: Face-to-face problem solving treatment

When the patient has not recovered from the guided self-help programme, a nurse from the department of Psychiatry offers a brief intervention: Problem Solving Treatment (PST). Earlier studies revealed that PST can be delivered by psychologists as well as nurses [22-24]. PST identifies problems that interfere with everyday functioning and that contribute to depression and anxiety. The treatment provides compensatory strategies that are designed to bypass the person's cognitive limitations and to improve adaptive functioning. PST comprises a short 6-session protocolled intervention. The first session takes 1 hour, the other sessions 45 minutes. PST is an evidence-based intervention for major depression and for psychological distress characterised by symptoms of depression and anxiety [22,23,25-28].

#### Step 4: Specialised psychological interventions such as cognitive behavioural therapy and/or antidepressant medication

In case all previous steps have not induced recovery, the patient chooses in close cooperation with the care coordinator between medication and psychotherapy. To ease this decision, the patient is offered the patient information letter of the Dutch College of General Practitioners on antidepressant medication. (A) If the patient chooses medication, the care coordinator contacts the patients’ physician who prescribes antidepressant medication and monitors outcomes. (B) If the patient chooses psychotherapy, the patient is referred to a psychologist or a psychiatrist. The stepped care programme is illustrated in Figure 1.

**Figure 1 F1:**
[figure not shown]
Overview of the stepped care programme.

#### Care as usual

Control group patients receive care as usual, which often means a single interview by a nurse or specialised intervention delivered by a social worker, psychologist or psychiatrist. In the context of the health economic evaluation, health care uptake is closely monitored, thus allowing for detailed post-hoc description of what usual care entailed exactly.

### Outcome assessment

#### Main outcome measure

The primary outcome measure is the Hospital Anxiety and Depression Scale (HADS). The Hospital Anxiety and Depression Scale (HADS) is a 14-item self-assessment scale for measuring symptoms of anxiety and depression and has been specifically designed for use in the medical ill. This scale has been proven to have adequate psychometrical properties and the total HADS score has been recommended for routine monitoring of psychological distress in cancer patients [29-32].

#### Secondary outcomes

Secondary outcome measures are health related quality of life questionnaires (EORTC QLQ-C30), EORTC QLQ-HN35, EORTC QLQ-LC13), general patient satisfaction (EORTC QLQ-PATSAT), and economic evaluation.

The EORTC QLQ-C30 is a tumour-specific, patient-based questionnaire. The questionnaire includes a global HRQOL scale (2 items) and comprises 5 functional scales: physical functioning (5 items), role functioning (2 items), emotional functioning (4 items), cognitive functioning (2 items) and social functioning (2 items). There are three symptom scales (fatigue (3 items), nausea, vomiting (2 items) and pain (2 items) and 6 single items relating to dyspnoea, insomnia, loss of appetite, constipation, diarrhoea and financial difficulties [33].

The EORTC QLQ-LC13 module covers specific issues on lung cancer. The questionnaire comprises 12 symptom scales: a 3 item scale on dyspnoea, and 1 item scales on coughing, haemoptysis, sore mouth, dysphagia, peripheral neuropathy, alopecia, pain in chest, pain in arm or shoulder, pain in other parts [33].

The EORTC QLQ-HN35 module covers specific issues on head and neck cancer. It has been used previously in studies. The questionnaire comprises 7 subscales: pain (4 items), swallowing (5 items), senses (2 items), speech (3 items), social eating (4 items), social contact (5 items) and sexuality (2 items). There are 10 single items covering problems with teeth, dry mouth, sticky saliva, cough, opening the mouth wide, weight loss, weight gain, use of nutritional supplements, feeding tubes, and painkillers [33,34].

The EORTC QLQ-PATSAT32 module is a patient satisfaction with care measure. The questionnaire comprises 4 scales on interpersonal skills (3 items), technical skills (3 items), information provision (3 items), and availability (2 items) of doctors, the same 4 scales regarding nurses, 1 scale on other hospital personnel kindness and helpfulness, and information giving (3 items), 1 scale on waiting time (2 items), 1 scale on access (2 items), and 3 single items on exchange of information, comfort/cleanness, and general satisfaction [35].

The economic evaluation will be conducted as a cost-utility analysis were outcomes are (changes in) health-related quality of life at patient level. Health-related quality of life is assessed with the EQ-5D [36,37] at baseline and 12 months follow-up. Direct medical and direct non-medical cost data are collected with the TIC-P [38], a widely used health service receipt interview in economic evaluations. Unit resource use (GP visits, hospital days, etc.) will be multiplied by their appropriate integral cost prices [39]. Indirect non-medical cost data related to production losses through work loss days and work cutback days will be sampled with the appropriate PRODISQ modules [40].

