**Methods/design:**

The study is designed as a randomized clinical trial with 2 treatment arms: a stepped care intervention programme versus care as usual. Patients treated for head and neck cancer (HNC) or lung cancer (LC) are screened for distress using OncoQuest, a computerized touchscreen system. After stratification for tumour (HNC vs. LC) and stage (stage I/II vs. III/IV), 176 distressed patients are randomly assigned to the intervention or control group. Patients in the intervention group will follow a stepped care model with 4 evidence based steps: 1. Watchful waiting, 2. Guided self-help via Internet or a booklet, 3. Problem Solving Treatment administered by a specialized nurse, and 4. Specialized psychological intervention or antidepressant medication. In the control group, patients receive care as usual which most often is a single interview or referral to specialized intervention. Primary outcome is the Hospital Anxiety and Depression Scale (HADS). Secondary outcome measures are a clinical level of depression or anxiety (CIDI), quality of life (EQ-5D, EORTC QLQ-C30, QLQ-HN35, QLQ-LC13), patient satisfaction with care (EORTC QLQ-PATSAT), and costs (health care utilization and work loss (TIC-P and PRODISQ modules)). Outcomes are evaluated before and after intervention and at 3, 6, 9 and 12 months after intervention.

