## Background

Every year more than 14,000 patients are diagnosed with cancer, of whom 11,470 with lung cancer (LC) and 2,870 with head and neck cancer (HNC) in the Netherlands [1]. Five-year survival rates are estimated at 13% in LC and 50% in HNC. Approximately 80% of the LC patients are male compared to 65% of the HNC patients. Patients often have to deal with devastating side effects of initial treatment (surgery, radiotherapy, and/or chemotherapy), such as pain, fatigue, and respiratory, speech and swallowing problems, negatively affecting health-related quality of life and associated with increased levels of psychological distress. Co-morbid anxiety or depression is present in 20-30% of LC and HNC patients [2-4]. During the first year after treatment there is a gradual improvement of psychological functioning [5,6] but many patients continue to suffer from or develop anxiety or depression [2,7-9].

Because of the overwhelming evidence of psychological distress in LC and HNC patients, intervention is recommended in national guidelines. Some recent reviews have shown evidence on efficacy of psychosocial intervention in cancer patients in general [10,11]. Others question evidence mainly because randomized trials are scarce [12,13] and because most studies included all patients even those without symptoms of depression and anxiety. Furthermore, it appears that most intervention studies are applied in patients with breast cancer. Patients with less prevalent tumours such as HNC or poor survival rates as in LC are often not involved, while LC and HNC patients are among the most distressed patients compared to cancer patients in general [14].

In clinical practice at present, many cancer patients who report high levels of psychological distress are not taking advantage of psychosocial care [14,15]. Barriers to admission to adequate psychosocial care are a lack of adequate screening of anxiety and depression in the often very busy oncology settings, reluctance by patients to be referred because of the already long treatment period, and that traditional models of the delivery of psychosocial care cannot meet current demand. Other forms of delivery, such as brief therapies, group treatments and self-help, and a stepped care approach may provide useful alternatives. Studies regarding cost-effectiveness of psychosocial intervention in cancer patients are scarce [16].

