## Methods/Design

### Design

In this prospective randomized controlled trial in two parallel groups, patients are recruited by screening all LC and HNC patients, who visit the Department of Pulmonary Diseases or the Department of Otolaryngology and Head and Neck Surgery of the VU University Medical Center in Amsterdam, the Netherlands, for follow-up consultation at least one month after treatment, for distress using a computerized touch screen data collection system (OncoQuest) or by telephone using the Hospital Anxiety and Depression Scale (HADS). All patients who fulfil the in- and exclusion criteria are asked to participate. After stratification for tumour site (LC vs. HNC) and stage (stage I-II versus III-IV), 176 participating patients are randomly assigned to the intervention or control group. In order to assess efficacy, assessment before and after intervention takes place and at 3, 6, 9, and 12 months follow up.

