### Statistical analyses

Descriptive statistics will be generated for the range of outcome variables, in particular to gauge whether randomization resulted in a balanced distribution of patients characteristics across the experimental conditions.

Repeated measures ANOVA will be used to determine the efficacy of intervention for continuous outcomes such as changes in HADS depression/anxiety symptom severity. Longitudinal changes over time in these variables will also be evaluation over all time points simultaneously using generalized estimating equations (GEEs). Analyses will be conducted in agreement with the intention-to-treat principle.

The economic data will be collected at baseline and follow-up and conducted as a cost utility analysis that is with health-related quality of life as the clinical endpoint. For the economic evaluation use will be made of the pertinent guidelines [39,44-46]. In other words, analyses will be conducted in agreement with the intention-to-treat principle; the societal perspective will be taken encompassing intervention costs, direct non-medical costs and indirect costs. Production losses will be economically valued using the friction cost method [47]. The time horizon will be set at one year, and therefore we will neither discount costs nor effects. Costs and effects will be analysed simultaneously, incremental cost-effectiveness ratios (ICERs) will be calculated and placed within 95% confidence intervals, 2,500 bootstrap replications of the ICERs will be projected on a cost-effectiveness plane, ICER acceptability curves will be plotted against different willingness-to-pay ceilings [48], and sensitivity analysis will be conducted as a matter of course focussing on uncertainty in the main cost-drivers. This will be done for the costs per QALY gained in a cost utility analysis.

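### The EQ-5D is scheduled only at baseline and 12 months, so the one-year QALY difference depends on a utility path that is never observed, and the abstract implies a different schedule

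*Protocol article*

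**What the plan says.** The only schedule given for the EQ-5D itself is in the protocol article under Secondary outcomes, in the paragraph on the economic evaluation: "Health-related quality of life is assessed with the EQ-5D [36,37] at baseline and 12 months follow-up". The Statistical analyses section is compatible with this: "The economic data will be collected at baseline and follow-up". It names no interim times.

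That section also fixes the horizon ("The time horizon will be set at one year"). After listing the incremental cost-effectiveness ratios, bootstrap and acceptability curves, it adds: "This will be done for the costs per QALY gained in a cost utility analysis".

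The abstract, under Methods/design, gives a different picture. It lists the EQ-5D among the secondary outcomes, "quality of life (EQ-5D, EORTC QLQ-C30, QLQ-HN35, QLQ-LC13", and then says of outcomes in general: "Outcomes are evaluated before and after intervention and at 3, 6, 9 and 12 months after intervention". The Design section gives the same visit pattern for efficacy: "assessment before and after intervention takes place and at 3, 6, 9, and 12 months follow up".

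The article does not say how utilities become QALYs.

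**The concern.** A QALY is the area under a utility curve. Two values fix the ends of the curve and say nothing about its shape. The economic conclusion therefore rests on an assumption about the months in between, although the trial already plans patient contacts in that period.

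This is a data-collection choice that the article states, so it is not a detail left open for an analysis plan. An analysis plan can choose how to interpolate, but it cannot recover utilities that were never collected. At stake are the QALY difference, the cost-effectiveness ratios and the acceptability curves built on it.

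A second defect lies in the text itself. The abstract and the Secondary outcomes section cannot both be right about when the EQ-5D is given.

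**Working it through.** **The plan's own figure.** There is none to reproduce: the article gives no EQ-5D value, QALY gain or utility difference. Its sample size rests on a standardised effect of 0.50 and plays no part here.

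**Inputs from the article.** EQ-5D at 0 and 12 months (Secondary outcomes); one-year horizon and cost per QALY (Statistical analyses); assessments at baseline, after intervention and at 3, 6, 9 and 12 months (abstract, Design).

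**Assumptions.** Linear interpolation between measurements; month 12 lies one year from baseline; between-arm utility differences d0, d3, d6, d9, d12 as shown below. The post-intervention assessment is left out because its calendar time depends on the steps a patient takes. The five-point result is itself an approximation to the true area, but it uses the visits that exist.

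**Formulas.**
- Two points: (d0 + d12)/2.
- Five points: 0.25 × (d0/2 + d3 + d6 + d9 + d12/2).

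**Results for an assumed peak difference of 0.08 and equal baselines.**

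| Assumed differences at 0, 3, 6, 9, 12 months | Five points | Two points | Two-point error |
|---|---|---|---|
| Transient: 0, 0.08, 0.08, 0.04, 0 | 0.25 × (0.08 + 0.08 + 0.04) = 0.050 | 0 | gain missed entirely |
| Early, sustained: 0, 0.08, 0.08, 0.08, 0.08 | 0.25 × (0.08 + 0.08 + 0.08 + 0.04) = 0.070 | 0.040 | 0.030/0.070 = 43% too low |
| Gradual: 0, 0, 0.04, 0.08, 0.08 | 0.25 × (0.04 + 0.08 + 0.04) = 0.040 | 0.040 | none |
| Seen only at month 12: 0, 0, 0, 0, 0.08 | 0.25 × 0.04 = 0.010 | 0.040 | four times too high |

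**Range.** For a peak difference g, the five-point results are 0.625g (transient), 0.875g (sustained) and 0.125g (month 12 only). The two-point results are 0, 0.5g and 0.5g. For g from 0.03 to 0.10:
- transient: 0.019 to 0.063 QALY against 0;
- sustained: 0.026 to 0.088 against 0.015 to 0.050;
- month 12 only: 0.004 to 0.013 against 0.015 to 0.050.

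The proportional error depends on the shape of the path and not on g.

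**The clock.** The abstract counts its 12 months from the intervention, while the horizon is one year. If the EQ-5D follows the abstract's clock, a patient who goes through step 1 (2 weeks) and step 2 (5 weeks) has the two values at least 2 + 5 = 7 weeks more than a year apart.

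**The case against.** The strongest reply is that the abstract may be the correct statement. The EQ-5D would then be collected at all six assessments, and only a wording error would remain. That cannot be ruled out, since the article condenses a fuller protocol. But the Secondary outcomes section is the specific statement and the abstract the general one, so the specific one is taken to govern until the sponsor says otherwise. Either way a passage must change.

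It is also fair to say that the article never commits to a straight line, and that the QALY formula and the handling of deaths and dropouts commonly belong in an analysis plan. This stands as a limit on the point: the linear formula is an assumption here. The lack of interim utilities does not depend on it. The article also gives no separate schedule for each EORTC questionnaire. What it does establish is that assessments take place at these times.

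Three stronger readings are tempting, and the article does not support them.

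- *The bias runs against stepped care.* A reader might infer this from a programme thought to act early. But the programme starts with 2 weeks without treatment, then 5 weeks of self-help, then six sessions of problem solving treatment, then step 4. Control patients may receive specialised help directly. The early difference could be absent or favour the control arm, and the table shows profiles with no error or an error in favour of stepped care.
- *Both arms recover anyway, so the difference is smallest at month 12.* The Background does say "During the first year after treatment there is a gradual improvement of psychological functioning", but the sentence goes on to say that many patients remain or become anxious or depressed. Its year runs from cancer treatment, whereas patients enter at least one month after treatment, with no upper limit stated.
- *A large share die within the year with only a baseline utility.* With the Background's five-year survival and a constant hazard, one could compute 1 − 0.13^(1/5) = 33.5% for lung cancer and 1 − 0.50^(1/5) = 12.9% for head and neck cancer. Those survival figures describe patients in general. The trial enrols treated patients who attend follow-up and are motivated for therapy, so their mortality cannot be derived from the article. For a death, moreover, the end value is known to be 0.

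**Conclusion.** The point holds in a limited form. As scheduled under Secondary outcomes, the EQ-5D gives a one-year QALY difference that cannot reflect anything between baseline and month 12, and the abstract disagrees with that schedule.

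The possible error is large relative to the quantity estimated, from complete loss of a transient gain to fourfold overstatement of a late one, and its direction is unknown. These sizes rest on linear interpolation and on assumed utility paths, since the article gives no utility values. If the true path is linear, or gradual as in the table, there is no error.

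The point concerns the secondary economic evaluation only. The HADS primary outcome, its repeated assessments and the sample size are untouched. It is worth acting on because the remedy is cheap and interim utilities cannot be collected afterwards.

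**What to change.** - Reconcile the abstract and the Secondary outcomes section by giving the EQ-5D at every assessment that already takes place: at baseline, after the intervention, and at 3, 6, 9 and 12 months. State whether months are counted from baseline or from the end of the intervention, and align this with the one-year horizon.
- Compute QALYs as the area under the utility curve at the actual assessment times, with utility 0 from death, and adjust the between-arm difference for baseline utility.

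The cost is a five-item questionnaire at four more assessments (after the intervention and at 3, 6 and 9 months) and a minor amendment. Patient burden is small. Interim values also keep some utility information on patients who leave before month 12, who would otherwise contribute a baseline value only.

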#### Sociodemographic and medical data

Next to the outcome measures, a case record form is developed including sociodemography (age, gender, social economic status), cancer and cancer treatment (TNM and ICD-10 classification, documentation of surgery and (chemo)radiation), and co-morbidity (Adult Comorbidity Evaluation 27 (ACE-27) test). The ACE-27 was designed specifically for cancer patients and classifies patients into 1 of 4 grades of comorbidity (none, mild, moderate, severe) [41].

